### **26.b Adjustments for primary and secondary outcomes**

To take into account the baseline prognostic factors at the cluster (school) level used for DA (c.f. Section Randomisation), all the results will be adjusted for language of the school, and the gender with three categories.

In case of imbalance for a variable at baseline, interaction and confounding effects will be tested according to its clinical significance.

Modification to protocol: Considering that immigration status has a very large protective effect on youth substance use (including in this sample), and that schools in Montreal vary significantly on this variable, we have modified the analysis plan to also include immigration status (immigrant, first generation, second generation) as a covariate.

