## 9. Randomisation

A dynamic allocation (DA) method will be used to allocate schools to intervention or control arms to balance baseline prognostic factors at the cluster (school) level. The Data Coordinating Centre statistician at Hôpital Sainte-Justine ([name], PI) generates randomization lists for school. The randomization process consists of computer-generated random lists of intervention allocations to school according to the Pocock–Simon modified minimization method to ensure balance across two covariates, the language of school (French, English) and the gender with three categories describing the proportion of boys in the school (< 25% boys, 25-75% boys, ≥ 75% boys). Details of the randomisation method are held securely at the Data Coordinating center (ACRU).

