**24.b Details on how baseline characteristics will be descriptively summarized**

At the school level, characteristics will include primary and secondary outcomes. At the individual level, variables include demographic variables as well as primary and secondary outcomes. The baseline characteristics of each group will be summarized as the mean, median, standard deviation, quartiles and range (min, max) for continuous variables; frequencies and percentages of individual/schools in each category for categorical variables.

It is expected that individual in the both collected allocated groups will, on average, be similar, given the randomization procedure.

Test of statistical significance will not be systematically done. Only descriptive data, as described above, will be presented. If substantial imbalance between randomization groups is identified in terms of any relevant variables not already being adjusted for in the primary analysis, additional adjusted sensitivity analyses may be performed.

**25. Outcomes****25.a Definition; Description and timing; Specific measurements and units; Any calculation or transformation; Used to derive an outcome**

See variable directory and Tables for description and timing.

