**26. Analysis methods****26.a Primary analysis methods used for the primary outcome**

The primary analyses will be the estimation of the effect of the intervention on substance use disorders in high-risk youth in intervention conditions relative to their control counterparts, at the year 5 follow-up (48 months post-intervention). The odds ratio (OR) will be used as the measure of intervention effect for the binary substance use disorders outcome. To account for within-cluster (school) variance, intervention effects will be examined using hierarchical generalized linear modelling (HGLM; using the SAS program, Proc GLIMMIX) using a Bernoulli distribution for the binary primary outcome. The HGLM model will be two-levels, with students as the first level, and nested within schools (clusters) as the second level of the model.

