##### model estimating linear growth over time #####
```

```
model_depado <- brm(Flagged ~ 1 + DEM_01 + Exp_Group + Language + year
+year:Exp_Group + (1|id+schoolnum),
data = cov_5,
family = bernoulli,
warmup = 1000,
iter = 3000,
cores = 4,
chains = 4,
seed = 123)
sum_model_depado<-summary(model_depado)
```

```

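### The posted primary-outcome model code lacks at least one covariate that SAP 26.b requires, without disclosure, and baseline DEP-ADO is not a covariate in either the SAP model or the code

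*Combined protocol and SAP*

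**What the plan says.** - **Allocation.** SAP section 9 minimises schools "to ensure balance across two covariates, the language of school (French, English) and the gender with three categories", the categories being bands of the proportion of boys in the school.
- **Required adjustment.** SAP 26.b (Adjustments for primary and secondary outcomes) carries both factors into the analysis: "all the results will be adjusted for language of the school, and the gender with three categories". The same section then records: "we have modified the analysis plan to also include immigration status (immigrant, first generation, second generation) as a covariate". Its stated reasons are that immigration status is very strongly protective against youth substance use, in this sample too, and that Montreal schools differ widely on it.
- **Other baseline variables.** 26.b provides for interaction and confounding tests where a baseline variable is imbalanced. Section 24.b allows extra adjusted sensitivity analyses if imbalance is substantial. Neither sets a threshold.
- **Primary model.** SAP 26.a: "The HGLM model will be two-levels, with students as the first level, and nested within schools (clusters) as the second level of the model". No baseline DEP-ADO term is named there or in 26.b.
- **Posted code.** The linear-time model begins "model_depado <- brm(Flagged ~ 1 + DEM_01 + Exp_Group + Language + year" and continues with a year-by-arm term and random intercepts for student and school. The categorical-time model has the same covariates.
- **Baseline data.** Section 19 makes reliable DEP-ADO data at baseline and year 5 a condition of mITT inclusion. Section 24.b summarises outcomes at baseline: "At the individual level, variables include demographic variables as well as primary and secondary outcomes".
- **Disclosure.** Item 6 of the closing list of deviations explains the move from a frequentist to a Bayesian multilevel model. It mentions no change of covariates.

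**The concern.** The plan commits to three covariates and the code has room for two. SAP section 4 says that analyses will strictly follow the plan and that departures will be identified. A covariate that disappears between plan and code, while the accompanying note describes only a change of statistical framework, is an undisclosed departure in the primary analysis.

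Either way, the missing covariate is one the plan itself treats as important: a factor used to allocate schools, or the variable it calls strongly protective. Leaving out a prognostic factor on which arms were balanced makes the usual test conservative and costs power.

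The baseline score is a second, smaller matter. It is already held and could recover some power. The plan instead leaves further adjustment to an imbalance rule without a threshold, and section 4 says the analyses are not blind to group. That gives discretion which a fixed covariate list would remove.

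**Working it through.** **1. Covariate count.** Required by 26.b: school language, three-category school gender mix, immigration status. Present in the code: `Language`, `DEM_01`.

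| If `DEM_01` is | Missing from 26.b's list | Minimisation factor missing? |
|---|---|---|
| school gender mix | immigration status | no |
| immigration status | school gender mix | yes |
| anything else, e.g. student sex | both | yes |

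The only other code of this family in the SAP, `DEM_06_Y1` in Appendix 3, is a student item (unauthorised absences). That makes a student-level `DEM_01` plausible, but does not establish it.

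**2. The plan's sample size.** Inputs from SAP section 10: p0 = 0.10, p1 = 0.05, k = 0.35, m = 50, 80% power, 2.5% error rate, here taken as one-sided.

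c = 1 + (1.96 + 0.8416)² × [(p0q0 + p1q1)/m + k²(p0² + p1²)] / (p0 − p1)²

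- Within-school term: (0.09 + 0.0475)/50 = 0.00275
- Between-school term: 0.1225 × 0.0125 = 0.00153
- c = 1 + 7.849 × 0.00428/0.0025 = 14.44, rounded up to 15 per arm

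This reproduces the plan's figure and uses no covariates. Power at 15 per arm is Φ(√(14 × 0.0025/0.00428) − 1.96) = 81.6%.

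**3. Baseline DEP-ADO.** Assumptions: m = 40 (20% of students lost, in line with the 80% final follow-up that protocol 2.14 reports for the earlier Adventure Trial) and a correlation r between baseline and the year-5 outcome, which the documents do not give. Adjustment multiplies the within-school term, 0.1375/40 = 0.00344, by (1 − r²).

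| r | Variance, within-school gain only | Power | Power if baseline also explains 10/30/50% of between-school variance (assumed) |
|---|---|---|---|
| 0 | 0.00497 | 76% | – |
| 0.2 | 0.00483 | 77% | 78% |
| 0.3 | 0.00466 | 78% | 82% |
| 0.4 | 0.00442 | 80% | 87% |

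At m = 50 the within-school gain alone takes 81.6% to 82.6%, 83.8% and 85.5%. Most of the larger gains in the last column at r = 0.3 and 0.4 come from the assumed school-level shares.

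A binary baseline flag would be weaker still. With an assumed 1% baseline prevalence and 10% at year 5, its correlation with the outcome cannot exceed √(0.01 × 0.90/(0.10 × 0.99)) = 0.30. The continuous score is the one to use.

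**4. Omitting a balanced school factor.** The documents give no effect size, so this is a simulated range: 15 + 15 schools, 50 students each, one binary school factor split almost evenly between arms, school SD 0.3 on the logit scale, and a school-level linear test at two-sided 5%. It illustrates the mechanism and is not the posted Bayesian model.

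| Factor log-OR | Type I error, factor omitted | Power, omitted | Power, included |
|---|---|---|---|
| 0 | about nominal | no loss | – |
| 0.5 | about 3% | 76–82% | 83–88% |
| 1.0 | about 1% | 58–61% | 84–88% |

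**The case against.** **`DEM_01` may be the school gender mix.** A reader might infer that an allocation factor has certainly been dropped. The documents do not support that. If `DEM_01` is the gender mix, both minimisation factors are present and only immigration status, which was not used for allocation, is absent. This stands, and the claim must stay conditional.

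**Baseline status may be in the model already.** A reader might infer that baseline DEP-ADO is ignored altogether. The data set `cov_5` is not described. If it holds the baseline wave, baseline status enters as an outcome row sharing the student's random intercept. SAP 26.b (Supplementary analysis methods) speaks of the 12 to 48 month points, which suggests otherwise but does not settle it. What is certain is that baseline is not a covariate.

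**Not adjusting for baseline is an efficiency choice, not an error.** This is fair. Protocol 2.6 times the intervention before natural onset in most Quebec youth, and protocol 1.1 gives 26.8% past-year alcohol use in Grade 7. A score near its floor may predict a Grade 11 threshold only weakly. The data have also been analysed, so adding baseline now is a choice made after the fact.

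**The effect on precision is easily overstated.** A reader might suppose that between-school variation dominates the standard error. Under the plan's inputs the within-school part is 64% of the variance at m = 50 (0.00275/0.00428) and 69% at m = 40. Nor does omission necessarily widen the interval: for a conditional odds ratio, adjustment mainly buys power and need not shrink the standard error of the log-odds ratio.

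None of this answers the count of three required covariates against two, or the silence in the list of deviations.

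**Conclusion.** The mismatch between plan and code is certain: at least one covariate required by 26.b is absent from both posted formulas and the omission is undisclosed. If `DEM_01` is not the school gender mix, a minimisation factor is missing. If it is not immigration status, the covariate that the SAP calls strongly protective is missing. The cost depends on how prognostic the omitted variable is. For a balanced school factor the simulated range runs from no loss to a substantial loss of power, with a conservative test and no inflation of false positives.

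The absence of baseline DEP-ADO as a covariate is also established, but it matters less. At m = 40 the within-school gain is roughly 1 to 4 percentage points of power for assumed r of 0.2 to 0.4, and larger only if baseline also explains differences between schools. All these figures rest on the plan's 10% versus 5%, k = 0.35 and 15 schools per arm, and on correlations and covariate effects that the documents do not supply.

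This should be corrected before the primary result is relied on. It does not by itself show that the result is biased.

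**What to change.** 1. Define `DEM_01`, and state which waves `cov_5` contains, in particular whether baseline is one of them.
2. Refit the primary model with every covariate in 26.b: school language, three-category school gender mix and immigration status. Report the posted version beside it as a disclosed deviation.
3. Add an analysis adjusted for the continuous baseline DEP-ADO score. Label it as added after the SAP because the data have already been analysed, and show it next to the version without that term.
4. Replace the imbalance-testing rule in 26.b with this fixed covariate set.

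The cost is a rerun on data already held, some SAP wording and a few model terms: two coefficients each for gender mix and immigration status where not already present, and one for the baseline score in the added analysis.

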### **26.c Planned sensitivity analyses**

Sensitivity analyses will be implemented to examine plausibility of putative mechanisms underlying the effectiveness of the intervention as well as the interaction between intervention and participants' characteristics.

Sensitivity 1: Replace missing data for the binary primary outcome using multiple imputation (section 27.a).

Modification to protocol: The senior investigator never intended to report primary outcomes without replacing missing data. This was an oversight at the time of finalising the first analysis plan. We therefore have agreed to report primary outcomes after having replaced missing data using a full information method with 20 imputations (see 27.a). Therefore, this procedure will be followed for the primary and secondary analyses, and not only for Sensitivity analysis 1.

Sensitivity 2: Test effect in HR students who indeed received the intervention rather than mITT (ie Per Protocol analysis)

Sensitivity 3: Interaction between HR status and Intervention effect – does the intervention effect reveal itself at a population level?

### **26.c Planned subgroup analyses**

Formal subgroup analyses were not planned in the protocol.

## **27. Missing data**

### **27.a Accounting for Attrition**

Each student will contribute annual observations until his/her end of follow-up (i.e. Grade 11). It is possible that attrition will be non-random or that some students may not show up for some of their annual assessments. To deal with such potential biases due to non-random attrition, individual annual observations will be re-weighted using the Inverse Probability of Weights (IPW), which will be estimated through HGLM model with a binary outcome (being present or absent at a given annual visit) based on the selected students baseline characteristics.

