### *2.14 What is the likely rate of loss to follow up? On what evidence is the loss to follow-up rate based?*

This trial protocol is much based on that of the Adventure Trial, which achieved an average follow-up rate across two treatment conditions and four follow-up periods of 84% (including the 2 schools unable to complete follow-

[name]. A cluster-randomised trial investigating the effects of selective intervention on adolescent cognitive development and addiction. Amount requested 1st year: \$242,556 Research Proposal up), with follow-up at the end of a two-year trial at 80%. We expect better follow-up in this trial, due to the less transient nature of a Montreal sample relative to a London sample, because participants will be recruited earlier in their academic career and required by law to be enrolled in school until the age of 16 years. Participation by school boards, rather than individual schools in London, will allow us to track students who transfer across schools while remaining in the trial. See Appendix D for recruitment and follow-up rates of the Adventure Trial[29].

*2.15 How many centers will be involved?* All recruitment will be conducted by CHU Ste Justine, U of Montreal, but University of Toronto and McGill will assist with data collection, management and analysis.

*2.16 What is the proposed type of analyses?*

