**23.b Reasons and details of school children withdrawal**

Most students drop out of a trial due to graduating from high school and moving to other schools, but this will not be a problem in this trial, as we do not expect to follow-up students beyond Grade 11. At the student level, the principal reasons of withdrawal are having left school (e.g. moving, conduct problems, academic difficulty). There are few cases of lost students because a school closed and one reported of death in the control condition.

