### **27.a Reporting and assumptions/statistical methods to handle missing data**

As missing primary outcome values (DEP-ADO scores at 48 months post-intervention) might depend on observed data and/or missing data, and due to the large amount of missing data for the binary primary outcome at 48 months post-intervention (see CONSORT flow diagram, Appendix 2), primary analysis will be performed with imputation for missing data using Multiple Imputation (MI). Missing data will be imputed under Missing At Random (MAR) assumption, and odds ratios estimates for each imputed data set will be obtained. The imputation will be repeated 20 times and Rubin's rule will be used to combine estimates and standard errors.

This represents a change to the original analysis protocol, which did not acknowledge that the potential bias in only considering data that from participants who were available for follow-up. Outcomes are expected to be affected by risk status and substance use outcomes, therefore intent-to-treat analysis will include all participants. Furthermore, as missing data is also at random and highly dependent on participant simply being present on the day of testing at school, there are also cases of missing data at only one timepoint of the 5 assessments. Omitting participants on the basis of one missing timepoint (i.e., listwise) would lead to very large attrition and lost data that would otherwise be useful in the evaluation of the outcome (either through estimate final outcome, or by providing outcomes at other timepoints).

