**Appendix 2: CONSORT diagram for the final study sample (Co-venture flow diagram)**

Figure 2. The percentages in this diagram represent the proportion of participants followed each year on the initial group size at baseline.

[figure not shown]

\*Missed participation: The participant was absent or refused to participate that specific year.

\*\*Lost to follow-up: The participant has left the school either for academic, conduct, moving reasons.

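### The missing-data plan for the 48-month SUD outcome adjusts at most in part for students who leave school after substance use, and no analysis tests departures from MAR

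*Combined protocol and SAP*

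**What the plan says.** **Weights.** SAP 27.a, Accounting for Attrition, accepts that attrition may be non-random. Its remedy is inverse probability weighting from a model for "being present or absent at a given annual visit) based on the selected students baseline characteristics". Baseline is Grade 7, age 12 to 13.

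**Imputation.** The second part of 27.a says missing 48-month DEP-ADO values "might depend on observed data and/or missing data" and calls the amount large. It then states "primary analysis will be performed with imputation for missing data using Multiple Imputation (MI" and "Missing data will be imputed under Missing At Random (MAR) assumption", with 20 imputations. The imputation predictors are not listed. It supports its approach by saying "as missing data is also at random and highly dependent on participant simply being present on the day of testing at school". SAP 26.c (sensitivity analyses) extends imputation to the primary and secondary analyses and lists no MNAR, delta or tipping-point analysis.

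**Leavers.** SAP 23.b says "the principal reasons of withdrawal are having left school (e.g. moving, conduct problems, academic difficulty". Appendix 2 defines lost to follow-up as "The participant has left the school either for academic, conduct, moving reasons", separately from students who were absent or refused in a given year.

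**Replacement.** Item 6 of the protocol-deviation list that closes the SAP reports that imputation did not converge and moves to a Bayesian multilevel model without imputed data. The printed model regresses the yearly SUD flag on a demographic variable, group, language, year and group by year, with random intercepts for student and school. It shows no weights, DEP-ADO score, SDQ, truancy or reason for leaving.

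**Analysis set.** SAP section 19 requires DEP-ADO data at baseline and year 5 for a child to enter the mITT. Section 27 says the intent-to-treat analysis includes all participants.

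**The concern.** A student who leaves over conduct or academic trouble is a different case from one who is away on the test day. The MAR argument in 27.a describes the second. For the first, the informative data are the later yearly measures: DEP-ADO score, SDQ conduct and hyperactivity, and self-reported truancy. The weights ignore them, the imputation text does not name them, and the final model uses only a binary flag that item 6 itself describes as sparse.

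The single primary endpoint is at stake. The programme targets substance use, and drop-out is itself a secondary outcome, so the link between use and leaving could plausibly differ by arm. If it does, the odds ratio is biased. Section 27 concedes that missingness may depend on the missing values, yet nothing planned would show how far the result depends on MAR.

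**Working it through.** **Inputs from the documents.** SUD 10% control and 5% intervention (SAP section 10). Planned OR = (0.05/0.95)/(0.10/0.90) = 0.474. The previous trial followed 80% at two years (Protocol 2.14). The 48-month rates of this trial are in a figure not available here, so 20% to 40% missing is assumed. The plan gives no figure for its attrition correction. Its 15 schools per arm is reproduced, 1 + 7.849 × [0.00275 + 0.35² × 0.0125]/0.0025 = 14.44, but the point does not depend on it.

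**Step 1: delta shift.** Start from the MAR risks and multiply the SUD odds of leavers by d. With fraction M missing, arm risk = (1 − M)p + M × [d·odds(p)/(1 + d·odds(p))]. Example: M = 20%, d = 3, intervention only. Leavers' risk = 0.1579/1.1579 = 0.1364. Arm risk = 0.8 × 0.05 + 0.2 × 0.1364 = 0.0673. OR = 0.0721/0.1111 = 0.649.

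| Missing | both arms, d = 2 / 3 | intervention only | control only |
|---|---|---|---|
| 20% | 0.477 / 0.483 | 0.565 / 0.649 | 0.400 / 0.352 |
| 30% | 0.477 / 0.484 | 0.611 / 0.739 | 0.370 / 0.310 |
| 40% | 0.477 / 0.485 | 0.658 / 0.831 | 0.344 / 0.276 |

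**Step 2: what completers show.** Let SUD multiply the odds of leaving by 2 or 3, with total leaving fixed at 20% to 40%. Completers' risk = p(1 − q1)/[p(1 − q1) + (1 − p)(1 − q0)], where q1 and q0 are the leaving probabilities with and without SUD. Equal dependence in both arms gives OR 0.466 to 0.471, but observed control prevalence falls from 10% to 8.56% and 7.57% (20% missing), or 7.44% and 5.98% (40%). Dependence in control only gives 0.562 to 0.827; in intervention only, 0.397 to 0.267.

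**Step 3: do weights help?** Simulation of 200,000 students × 8 runs, about 24% missing, with a binary baseline factor and a binary interim SUD history.

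| Leaving follows | full data | completers | baseline weights | baseline + history weights |
|---|---|---|---|---|
| earlier observed SUD, odds × 5, control only | 0.449 | 0.480 | 0.479 | 0.446 |
| same, intervention only | 0.449 | 0.428 | 0.429 | 0.449 |
| unobserved 48-month SUD, × 3, control only | 0.446 | 0.664 | 0.665 | 0.658 |
| same, intervention only | 0.447 | 0.302 | 0.303 | 0.304 |

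Baseline weights reproduce the completers' result. History removes the part of the bias that follows recorded use. No MAR method removes the last two rows.

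**Step 4: the replacement model.** Simulation with a continuous liability: 36-month to 48-month correlation about 0.75, final prevalence 10% v 5%, leaving logit −1.5 + 0.8 to 1.0 × 36-month score, arm interaction −0.5 to −1.0, about 17% to 22% leaving, school effects omitted. True marginal OR is 0.47 to 0.48. Completers give 0.56 to 0.71, and baseline weights 0.55 to 0.70. Weights that include the 36-month score give 0.47 to 0.48. A random-intercept logistic model on the yearly flags, as a stand-in for the printed model, gives marginal ORs of 0.49 to 0.57. At the top of the range it removes (0.71 − 0.57)/(0.71 − 0.48) = 61% of the bias. With equal dependence in both arms it gives 0.45 to 0.47, with control prevalence about 8.5% instead of 10%.

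**The case against.** The best defence is that the weights are not the primary method. Sections 26.c and 27.a name multiple imputation, and 27.a values students who supply outcomes at other time points. The reported model then uses each student's observed flags from other years, so it does borrow from recorded substance use under MAR. This stands. A reader might infer that the 48-month odds ratio is wholly uncorrected for substance-related withdrawal. The documents do not support that; in step 4 the flag-based model removes roughly three-fifths to two-thirds of the bias.

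A reader might also infer that the odds ratio must be pulled toward 1. That needs leaving to follow use more steeply in the control arm. The text gives no leaving by use or by arm, and the reverse pattern moves the odds ratio away from 1.

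Two further inferences fail. Protocol 2.14 expects that school-board participation "will allow us to track students who transfer across schools while remaining in the trial", but this is a forecast, and the Appendix 2 wording is a footnote to a figure not available here. It cannot be said that traced transfers were counted as lost. Nor is the reason for leaving shown to be recorded per student, since Appendix 2 pools moving, conduct and academic reasons.

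The defence does not answer the absence of any MNAR analysis, the reliance on a sparse flag when richer yearly scores exist, or the conflict between sections 19 and 27.

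**Conclusion.** The concern holds as an incomplete correction and an untested assumption, not as a demonstrated bias. Baseline-only weights do almost nothing for leaving that follows later substance use. The imputation text cannot be judged because its predictors are unlisted. The replacement model corrects in part.

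A material effect on the odds ratio requires the link between use and leaving to differ by arm. Under the assumed inputs of step 1, the odds ratio then lies anywhere from 0.276 to 0.831 against a planned 0.474, in either direction. With equal dependence it hardly moves, and the damage is to the reported SUD prevalence. The size depends heavily on what drives leaving: in step 3 the shift is about 0.03 or less when leaving follows an earlier binary flag, and about 0.15 to 0.22 when it follows the unobserved 48-month outcome in one arm. The documents do not show which applies, which is the reason for a tipping-point analysis.

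**What to change.** 1. In the missing-data method actually used, bring in prior-wave DEP-ADO score, SDQ conduct and hyperactivity, self-reported truancy, and the arm by prior DEP-ADO interaction. In the Bayesian model these belong in a joint or auxiliary model. Entered as plain covariates of the treatment contrast, they would condition on post-randomisation use and change the effect being estimated.
2. State in section 27 that the final method is the Bayesian model. Either drop the weighting step or label it a sensitivity analysis with prior-wave predictors.
3. Add an arm-specific delta analysis for students who left school, separate from those absent on the day, and report the tipping point. Split by reason only if reason is recorded per student.
4. Reconcile section 19 (year-5 DEP-ADO required) with section 27 (all participants included), so that leavers are in the analysis set.

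The yearly measures and the split between leavers and absentees already exist. The cost is SAP wording, somewhat more variable estimates and one more sensitivity table.
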